### Adverse events

It is anticipated that no adverse effects due to the training will occur. This is consistent with trials on caregiver training around the world.

### Outcome measures

The primary outcomes are CG stress (subjective burden [31,32], role overload [33], and cortisol), perceived benefits (from open-ended questions), subjective health [34], psychological well-being [35,36], and depression [37,38]. The secondary outcomes are CG coping [39], and CR’s BPSD [40,41] and functional impairment [42,43]. Same for group and individual interventions, all outcome measures, except cortisol, will be obtained at baseline (0 month; T1), post-treatment (2 months; T2), and 6 (T3), 12 (T4), 18 (T5) and 30 months (T6). Salivary cortisol, collected using the Salivette five times during the day (immediately after awakening, 30 minutes post-awakening, 45 minutes post-awakening, and at 11:00 and 21:00) for two consecutive days, will be obtained at T1-T4 only. This design will allow an assessment of the long-term effects of the interventions. The last assessment (T6) is not only necessary to assess the more long-term impacts of the treatment, but is spaced out at a longer interval in order to provide a more stringent test of the effects of the treatment. It is possible that the half-yearly assessment conducted from six months onward may serve as soft reminders for benefit searching, from which the benefit group may gain more. The 12-month interval from T5 to T6 eliminates this possibility and enhances the generalizability of the findings to naturalistic settings. Data analysis will be performed using the principle of intent-to-treat, and missing values will be estimated by multiple imputations using Markov chain Monte Carlo method.

### Study hypotheses

We expect that participants in the benefit-finding group will report more benefits, lower burden, lower overload, better subjective health, better psychological well-being, and lower depression than both the psychoeducation and the simplified psychoeducation group, whereas the latter two would not differ from each other. For cortisol, the benefit-finding group is expected to have a steeper slope of diurnal decline and lower cortisol level at 21:00 than the other two groups. With respect to cortisol in the awakening period, the benefit-finding group is expected to have higher levels at 0, +30 and +45 minutes post-awakening than the other two groups. We also predict an improvement in CG coping, CR BPSD, and a slower rate of decline of CR functional impairment for the benefit-finding group, over the other two groups, over time.

### Statistical analysis

The data structures contain multiple levels. For Trial 1, repeated measurements (level 1) is nested within persons (level 2), which then is nested with the cluster (level 3) from which they were recruited. For Trial 2, the data contain the first two levels only. Because of the multilevel structure, data will be analyzed using mixed-effects regression with full-information maximum-likelihood estimation in Stata version 11.1. This procedure does not require imputation of missing data common in longitudinal studies because the conditional distribution of missing data based on data observed are incorporated into estimation of parameters [44].

In mixed-effects regression, the intercepts and effect of time (centered) will be specified to vary randomly at cluster (Trial 1) and person (both Trial 1 and Trial 2) levels. Two dummies will be created for the treatment groups with simplified psychoeducation as the reference category. Thus the effects of benefit-finding and psychoeducation will be compared against simplified psychoeducation in the first set of analyses. Product terms of benefit-finding x time and psychoeducation x time will be created to test whether changes in the outcome measures over time are different from those of the simplified psychoeducation group. Additional analyses will be conducted by dropping participants in the simplified psychoeducation condition while coding psychoeducation as the reference group, so that the effects of benefit-finding can be compared directly with psychoeducation as well. In this case, only two treatment groups will be included in the analyses.

With six repeated measurements (month 0, 2, 6, 12, 18, and 30), a medium treatment by time interaction effect (Cohen’s *d* = 0.50), power = 0.80, two-tailed alpha = .017 (Bonferroni-corrected for multiple comparison among three treatment groups), ratio of time-effect variance at person-level to the sum of random-intercept variance and time-level residual variance = 0.20 (which is quite large to yield conservative estimates of power), 17 participants per experimental condition are sufficient, no matter whether there are two or three experimental conditions in the regression analysis. For the cluster-randomized controlled trial, with the addition of the ratio of time-effect variance at home-level to the sum of random-intercept variance and time-level residual variance = 0.02, four homes per condition and 10 participants per home are adequate, regardless of whether there are two or three experimental conditions in the regression analysis [45,46].

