### Randomization and masking

A computer software generating true random numbers will be used for assigning participants into interventions. For Trial 1, participants will be randomized by center or clinic (that is, participants recruited from the same setting will be randomized in one unit). For Trial 2, participants will be randomized individually. In both trials, participants will be told on the consent form that they would receive ‘a course related to the caring of patients with dementia,’ without being told the different interventions. The trainers will not be used as interviewers so as to ensure that the interviewers are blind to the participants’ assignment status as well. Hence, both trials are double-blind randomized controlled trials, but Trial 1 differs from Trial 2 in being a cluster trial.

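### Trial 1's four clusters per arm reach 0.80 power only on normal quantiles; a between-cluster t test that holds its level has about 0.72 (three arms) or 0.62 (two arms), and no small-sample correction is stated

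*Protocol article*

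**What the plan says.** Protocol article, Randomization and masking: "For Trial 1, participants will be randomized by center or clinic".

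Statistical analysis, sizing paragraph: the target is "power = 0.80, two-tailed alpha = .017", the level being Bonferroni-corrected for three groups. The effect is a treatment-by-time interaction of d = 0.50 over six visits (months 0, 2, 6, 12, 18 and 30). The person-level input is "ratio of time-effect variance at person-level to the sum of random-intercept variance and time-level residual variance = 0.20"; the corresponding cluster-level ratio is 0.02. The result is 17 participants per condition without clustering. For Trial 1, "four homes per condition and 10 participants per home are adequate, regardless of whether there are two or three experimental conditions". I read homes as the randomized clusters: 3 × 4 × 10 = 120, the Trial 1 target under Participants.

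Statistical analysis, model paragraphs: "data will be analyzed using mixed-effects regression with full-information maximum-likelihood estimation in Stata version 11.1", with random intercepts and time effects at cluster and person level. The first model holds all three arms. Benefit-finding versus psychoeducation is then tested after dropping the simplified arm. No reference distribution or small-sample correction is given.

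**The concern.** With 12 clusters in three arms, the between-cluster variance rests on 12 − 3 = 9 degrees of freedom; with one arm dropped, on 8 − 2 = 6. At a level as strict as 0.017 this matters, because the critical value rises from 2.39 (normal) to 2.92 (t, 9 df) or 3.27 (t, 6 df). Sizing that ignores this overstates power, and the statement that the number of arms in the model makes no difference cannot hold.

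Full maximum likelihood adds to the problem. It does not correct the cluster-level variance for the estimated arm effects, so that component comes out at roughly 9/12 or 6/8 of its proper value. If the contrast is then referred to a normal distribution, the Bonferroni level is not held.

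At stake are the Trial 1 p-values and intervals, and above all the benefit-finding versus psychoeducation contrast, which Study objectives presents as the test of whether the benefit-finding component is useful.

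**Working it through.** **Inputs (Statistical analysis).** Two-sided alpha 0.017; power 0.80; d = 0.50; slope-variance ratios 0.20 (person) and 0.02 (cluster); 4 clusters of 10 per arm. The time unit of d is not stated.

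**Step 1: reproduce the plan's figures.** z(0.9915) + z(0.80) = 2.387 + 0.842 = 3.228, and 3.228² = 10.42.

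- Individual design: n = 2 × 10.42 × 0.20 / 0.50² = 16.7, rounded up to 17.
- Cluster design: K = 2 × 10.42 × (0.02 + 0.20/10) / 0.50² = 3.34, rounded up to 4.

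Both match. The level-1 residual adds at most 1/637.3 = 0.0016 to the slope variance when time is in months (637.3 is the centred sum of squares of the visit times), giving 16.8 and 3.35, so it is negligible. Other time units tried (years, visit index, 0–1 scale, end-of-study difference) do not give 17 together with 4; in years, for example, n is 22 to 36. The per-month reading and the normal quantiles are therefore inferred from this match.

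**Step 2: power at four clusters per arm.** SE = √[(2/4) × (0.02 + 0.20/10)] = √0.02 = 0.1414. Noncentrality = 0.50 / 0.1414 = 3.54.

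| Reference | Critical value | Power |
|---|---|---|
| Normal | 2.387 | 0.87 |
| t, 9 df (three arms) | 2.921 | 0.72 |
| t, 6 df (two arms) | 3.272 | 0.62 |

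With five clusters per arm the t-based figures are 0.86 and 0.80.

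**Step 3: false-positive rate if maximum likelihood is paired with z.** Simulation used 400,000 balanced data sets per setting, complete data, person-level slope variance 0.20 and cluster variance bounded at zero. Nominal level 0.017:

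| Cluster slope ratio | Three arms | Two arms |
|---|---|---|
| 0 | 1.8% | 1.8% |
| 0.005 | 2.8% | 2.9% |
| 0.01 | 3.8% | 3.8% |
| **0.02 (plan)** | **5.2%** | **5.5%** |
| 0.04 | 6.2% | 7.0% |

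At nominal 0.05 and ratio 0.02 the rates are about 10.4% and 10.7%.

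**Step 4: alternatives at ratio 0.02, nominal 0.017.** The t reference uses clusters-minus-arms df.

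| Test | Level, three / two arms | Power, three / two arms |
|---|---|---|
| Cluster-level summaries, t | 1.7% / 1.7% | 0.72 / 0.62 |
| REML, t | 1.2% / 0.7% | 0.72 / 0.61 |
| ML, t | 2.0% / 1.1% | 0.82 / 0.72 |

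**The case against.** A reader might infer that Trial 1's false-positive rate will be three times nominal. The article does not support that as a fact. It fixes the estimator but never says that arm contrasts are referred to z, and an article may leave that choice to the analysis plan. With maximum likelihood kept as written and a t reference used, the rate is 2.0% or 1.1%. The inflation also depends on the cluster slope ratio, from about 1.1 times nominal at 0 to about 4 times at 0.04, and 0.02 is a planning value, not an observation. At nominal 0.05 it is about twofold. So the inflation is conditional on z.

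On power, maximum likelihood with t reaches 0.82 in the three-arm model, though at a level slightly above 0.017. It would thus be wrong to say that every reasonable test falls short there. In the two-arm subset it gives 0.72, still below 0.80. At a cluster ratio of 0.01 even the cluster-level t test has 0.85 and 0.76. The 0.62 belongs to what the article calls additional analyses.

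The number of clusters actually recruited is not reported, so 9 and 6 df follow from the sizing statement. The per-month reading of d is inferred, and the sources cited for the sizing method are not at hand.

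These points limit the claim but do not remove it. The level, cluster number, target power and indifference to the number of arms are all stated. A later plan that added small-sample df would protect the level but would leave the power claim for a level-holding between-cluster test uncorrected.

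**Conclusion.** The point holds in two parts of different strength.

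The power statement is wrong as it stands. Four clusters per condition follow from normal quantiles. On the same inputs, a between-cluster t test that holds 0.017 has power of about 0.72 in the three-arm model and 0.62 in the benefit-finding versus psychoeducation subset. Dropping an arm therefore costs about 10 percentage points. This rests on d as a slope difference per month, a negligible level-1 residual, balanced clusters of 10 and the planned ratios; it needs no assumption about which reference distribution the trial will use.

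The false-positive part is conditional. If maximum-likelihood contrasts are referred to z, a nominal 0.017 test rejects about 5% of the time at the planned ratio, which in effect undoes the Bonferroni correction. The article states nothing that would prevent this, but it does not state that it will happen.

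**What to change.** For Trial 1, prespecify one of the following:

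- an analysis of cluster-level summaries with a t test on clusters-minus-arms df, which holds 1.7% when clusters are balanced; or
- REML with between-cluster, Satterthwaite or Kenward-Roger df. With clusters-minus-arms df it is somewhat conservative here (about 0.7 to 1.2%), which should be acknowledged. REML uses incomplete profiles under the same missing-at-random assumption as full maximum likelihood.

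Restate Trial 1 power as about 0.72 (three-arm model) and 0.62 (two-arm subset) on the plan's inputs, withdraw the statement that the number of arms makes no difference, and give the time unit of d.

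The cost is wider Trial 1 intervals and a less favourable stated power. No extra clusters are needed. Trial status reports 112 participants recruited to Trial 1 by January 2012 and completion expected around May 2014, so on that timetable the analysis wording could still be changed during follow-up.

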### Study objectives

The purpose of this randomized controlled trial is to evaluate the effectiveness of a new, multicomponent intervention combining psychoeducation with benefit finding. Two control groups will be used. First, in order to ascertain whether the benefit-finding component is useful, this intervention will be evaluated against a ‘pure’ psychoeducation program. However, the psychoeducation group used in this study is strictly speaking not a treatment-as-usual control because it is far more in-depth and comprehensive than the psychoeducation programs offered by service agencies in developing countries in this region, which typically are brief (for example, consisting of a few sessions) and focused on information provision (that is, education) only. From both scientific and policy points of view, a second control group that more closely mimics the existing services is needed. Thus, a simplified psychoeducation program focused only on information provision is created for this purpose. This allows the benefit-finding intervention to be evaluated against the form of psychoeducation that is commonly reported in the mainstream, Western literature as well as against the version of psychoeducation that is commonly found in this region. Trial 1 will evaluate the interventions in group settings (for example, social centers, clinics), whereas in Trial 2, the interventions will be conducted individually in the caregivers’ own homes. These two trials together permit an assessment of the effects of the interventions in different modes of delivery.

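### In Trial 1, comparing benefit-finding with psychoeducation by refitting without the third arm leaves 8 rather than 12 clusters to estimate the variance; a contrast in the three-arm model keeps all 12

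*Protocol article*

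**What the plan says.** The Study objectives section of the protocol article gives the comparison with full psychoeducation a specific job: "in order to ascertain whether the benefit-finding component is useful, this intervention will be evaluated against" a psychoeducation-only programme. The Study hypotheses section then predicts a difference on the benefit, burden, overload, health, well-being and depression outcomes.

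The Statistical analysis section first sets up a mixed-effects model with all three arms: two arm indicators, simplified psychoeducation as reference, and the product of each indicator with time. Intercepts and time effects vary randomly by person and, in Trial 1, by cluster. Estimation is by full-information maximum likelihood. Benefit-finding is then set against psychoeducation in additional analyses, by "dropping participants in the simplified psychoeducation condition while coding psychoeducation as the reference group". The section adds: "In this case, only two treatment groups will be included in the analyses". The only reason given is that this allows a direct comparison of the two arms.

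The sample-size paragraph uses "power = 0.80, two-tailed alpha = .017" and calls the numbers adequate whether two or three conditions are in the model.

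**The concern.** The direct comparison needs no second model. In the three-arm model it is the benefit-finding coefficient minus the psychoeducation coefficient, and likewise for the two product terms. Changing the reference category with every arm kept gives the same thing.

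The refit gives up the third arm's contribution to the pooled variance components. That contribution matters where clusters are few. Trial 1 plans four clusters per arm, so the refit asks 8 clusters instead of 12 to support a cluster-level random intercept and slope. The comparison affected is the one meant to show whether the new component adds anything.

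**Working it through.** **Inputs (Statistical analysis section).** Two-sided alpha 0.017; power 0.80; d = 0.50 for "a medium treatment by time interaction effect"; visits at 0, 2, 6, 12, 18 and 30 months; "ratio of time-effect variance at person-level to the sum of random-intercept variance and time-level residual variance = 0.20"; the corresponding cluster-level ratio 0.02; ten participants in each of four clusters per arm in Trial 1. The recruitment targets (Participants section) are 120 and 100.

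**Assumptions.** Equal arms and clusters and no dropout. The share of variance due to the random intercept, ρ, is not given; 0 to 0.9 was tried, and 0.5 is used below.

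**Step 1: reproduce the plan's figures.** The sum of squared centred times in months is S = 1408 − 68²/6 = 637.33. The normal quantiles are 2.387 and 0.842, with sum 3.228, so 2 × 3.228² / 0.50² = 83.4.

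- Individual trial, n per arm: 83.4 × [(1 − ρ)/S + 0.20] = 16.69 to 16.81 over the range of ρ, rounded up to the stated 17.
- Cluster trial, clusters per arm: 83.4 × [(1 − ρ)/(10S) + 0.20/10 + 0.02] = 3.34 to 3.35, rounded up to the stated 4.

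Time in months is the scale that reproduces 17. Visit number gives 18 to 22, and years give 19 to 36. The formula uses normal quantiles, which is why the plan's answer does not depend on the number of arms in the model.

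**Step 2: Trial 1 with a small-sample t test.** The variance of the slope difference is 2 × [0.5/6373.3 + 0.02 + 0.02]/4 = 0.02004. The noncentrality is 0.50/√0.02004 = 3.53. Degrees of freedom are clusters minus arms.

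| | Three-arm contrast | Two-arm refit |
|---|---|---|
| Clusters | 12 | 8 |
| df | 12 − 3 = 9 | 8 − 2 = 6 |
| Critical t, alpha 0.017 | 2.92 | 3.27 |
| Power | 0.72 | 0.62 |

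The interval is wider by 3.27/2.92 = 1.12. If the noncentrality is instead set at 3.228, which gives exactly 80% power under normal quantiles, power is 0.63 against 0.53, so the gap is again about ten points.

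**Step 3: Trial 1 with maximum likelihood and normal quantiles.** The critical value is 2.387 in both fits and power is Φ(3.53 − 2.387) = 0.87 in both, so no power is lost. But maximum likelihood shrinks the between-cluster variance by about df divided by clusters, which is 9/12 = 6/8 = 0.75. The effective cut-off is 2.387 × √0.75 = 2.07 in both fits. Against t with 9 df this gives a type I error of about 0.069; against 6 df, about 0.084. Nominal is 0.017.

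**Step 4: Trial 2.** With about 33 per arm, df are 100 − 3 = 97 against 66 − 2 = 64, critical values 2.43 and 2.45, and power 98.1% and 98.0%. At the planned minimum of 17 per arm, df are 48 and 32, and power is 77.9% and 76.4%.

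**The case against.** The strongest reply is that the power loss belongs to a test the plan does not specify. The plan names maximum likelihood, states no small-sample degrees of freedom, and its sample sizes reproduce with normal quantiles. On that footing power is the same in both fits. This stands, and the ten-point loss must not be reported as a property of the plan as written. What the plan loses on that footing is error control. Most of that inflation comes from having few clusters; dropping the arm makes it worse, from about 0.069 to 0.084.

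Four stronger readings are tempting but not supported:

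- **That the two-arm estimate is biased or will contradict the main model.** With balanced, complete data the point estimates coincide. They can differ only through imbalance or missing data.
- **That the third arm informs the time profile of the other two.** Each arm has its own intercept and slope through the indicators and product terms. The third arm helps only through the pooled variance components.
- **That both trials are affected.** Step 4 shows that Trial 2 hardly changes.
- **That dropping the arm gains nothing, so the refit should be deleted.** The refit does not require the third arm to share the others' variance. In simulation with the third arm's cluster variance at 0.25 or 4 times that of the others, the pooled t test had type I error 0.036 or 0.004, while the two-arm test stayed at 0.017. At 4 times, pooled power was 0.40 against 0.62. A lecture-only arm could plausibly differ in variance. The article does not give this reason, and it mentions no arm-specific variances and uses single variance ratios. That supports keeping the refit as a check, not as the main estimate.

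**Conclusion.** The concern holds for Trial 1 and is one of efficiency and error control, not validity. The refit takes 3 of 9 between-cluster degrees of freedom from a central comparison when the main model already supplies it. The cost is about ten power points and a 12% wider interval under a small-sample t test, or a rise in approximate type I error from 0.069 to 0.084 under maximum likelihood with normal quantiles.

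The fall from 9 to 6 df rests only on four clusters per arm and the clusters-minus-arms rule. The absolute power figures rest on more: the month scale that reproduces 17 implies an effect of 0.5 SD per month, or 0.5 × 30 = 15 SD over follow-up, so they illustrate the loss and do not forecast the trial's power. The type I error figures are approximations for balanced data. All comparisons in steps 2 to 4 assume a variance common to the arms.

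**What to change.** Make the main estimate of benefit-finding minus psychoeducation a linear contrast, for both the arm terms and the time-product terms, in the single three-arm model for each outcome. Equivalently, change the reference category with all arms kept in.

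In Trial 1, add small-sample inference, for example restricted maximum likelihood with between-cluster degrees of freedom. The contrast alone does not restore error control, and restricted maximum likelihood with normal quantiles would still give a type I error of about 0.041 with 12 clusters.

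Keep the two-arm fit as a labelled sensitivity analysis, which would show whether the third arm's variance is driving the result.

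The cost is one post-estimation contrast per outcome and a changed reference distribution in Trial 1. No new data are needed. The small downside is reliance on a variance common to all three arms, which the main model already assumes.

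### The sample sizes of 17 per condition and 4 homes x 10 equal a calculation on slope variance alone; with no time unit for d and no residual share stated, 80% power for a medium effect is not supported

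*Protocol article*

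**What the plan says.** The sample-size paragraph (Protocol article, Statistical analysis) sets these inputs:

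- Schedule: "With six repeated measurements (month 0, 2, 6, 12, 18, and 30").
- Effect: "a medium treatment by time interaction effect (Cohen’s *d* = 0.50").
- Error rates: "power = 0.80, two-tailed alpha = .017", the alpha being 0.05 divided among three group comparisons.
- Person-level slope variance: 0.20 of the sum of intercept and residual variance, described as a value "which is quite large to yield conservative estimates of power".
- Home-level slope variance in the cluster trial: 0.02 of the same sum.

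It concludes that "17 participants per experimental condition are sufficient, no matter whether there are two or three experimental conditions in the regression analysis", and for the cluster trial that "four homes per condition and 10 participants per home are adequate".

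The same section plans a mixed model with random intercepts and random time effects, in which treatment-by-time product terms test whether change differs between groups. The Participants section plans 120 caregivers for Trial 1 and 100 for Trial 2.

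**The concern.** The tested quantity is a difference in slopes. Its variance in the planned model has two parts: the variation of true slopes between people (and homes), and the error in estimating each person's slope, which is the residual variance divided by the sum of squared deviations of the visit times. The first part alone already yields the stated sizes. The second is negligible or dominant depending on the unit in which time, and therefore d and the 0.20 ratio, is measured. The paragraph gives no unit. It uses residual variance only in the denominator of its ratios and does not say what share of that denominator it makes up.

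A reader will take the paragraph to mean that each trial has 80% power to detect a conventional medium difference. If that is not so, a null result could be misread as evidence against such a difference.

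**Working it through.** **Inputs from the document:** two-sided alpha 0.017, power 0.80, d = 0.50, slope-variance ratios 0.20 (person) and 0.02 (home), 10 people per home, visits at 0, 2, 6, 12, 18 and 30 months, planned totals 120 and 100.

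**Assumptions:** equal allocation (100/3, about 33 per arm in Trial 2; 120 = 3 x 4 x 10 in Trial 1); d in units of the SD formed by intercept plus residual variance; residual share r of that sum not given, so varied over 0.3, 0.5 and 0.7.

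**Step 1: reproduce the stated figures.** z(0.9915) = 2.387, z(0.80) = 0.842 and (2.387 + 0.842)^2 = 10.42, so the multiplier is 2 x 10.42/0.50^2 = 83.38.

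- Individual trial: 83.38 x 0.20 = 16.7, giving 17 per arm.
- Cluster trial: 83.38 x (0.02 + 0.20/10) = 3.3, giving 4 homes per arm.

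Both match with no residual term.

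**Step 2: add the residual term.** With SS the sum of squared deviations of the visit times:

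- n per arm = 83.38 x (0.20 + r/SS)
- homes per arm = 83.38 x (0.02 + 0.20/10 + r/(10 x SS))

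In months, the squared times sum to 1408 and the times to 68, so SS = 1408 - 68^2/6 = 637.3. In years, SS = 637.3/144 = 4.43. With 30 months as one unit, SS = 637.3/900 = 0.708. With visits numbered 0 to 5, SS = 17.5.

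**Step 3: results by time scale** (r = 0.3 / 0.5 / 0.7, normal quantiles).

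| Unit of time | Meaning of d = 0.50 by month 30 | n per arm needed | Power, 33 per arm | Power, 4 x 10 |
|---|---|---|---|---|
| Month | 15 SD | 17 / 17 / 17 | 98 / 98 / 98% | 87 / 87 / 87% |
| Visit | 2.5 SD | 19 / 20 / 21 | 98 / 97 / 96% | 86 / 85 / 84% |
| Year | 1.25 SD | 23 / 27 / 30 | 94 / 89 / 84% | 81 / 77 / 73% |
| 30 months | 0.5 SD | 52 / 76 / 100 | 57 / 40 / 30% | 53 / 40 / 31% |

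Worked example for the last row at r = 0.5: V = 0.20 + 0.5/0.708 = 0.906, so n = 83.38 x 0.906 = 75.5, giving 76. At 33 per arm the standard error is sqrt(2 x 0.906/33) = 0.234, and power = Phi(0.5/0.234 - 2.387) = 40%.

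**Step 4: how much residual the stated sizes tolerate.**

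- For 17 per arm, r can be at most (17/83.38 - 0.20) x SS. That is 0.3% on the 30-month scale, 1.7% per year, 6.8% per visit, and any share per month.
- For 4 homes, r can be at most (4/83.38 - 0.04) x 10 x SS. That is 5.6% on the 30-month scale, 35% per year, and any share per visit or per month.

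**Step 5: what month coding implies.** d = 0.50 per month is 0.50 x 30 = 15 SD at month 30. The 0.20 ratio is a slope SD of sqrt(0.20) = 0.45 per month, or 13.4 SD over the trial.

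**Step 6: small-sample reference, even with r = 0.** Replacing normal quantiles by a t distribution gives about 77% power at 17 per arm (32 df) and 62% at 4 homes per arm (6 df).

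**Step 7: detectable difference at month 30 with 80% power** (30-month scale, normal quantiles, r = 0.3 / 0.5 / 0.7).

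- 33 per arm: sqrt(2 x 10.42 x V/33), with V = 0.624 / 0.906 / 1.189, gives 0.63 / 0.76 / 0.87 SD.
- 4 x 10: sqrt(2 x 10.42 x Vc/4), with Vc = 0.082 / 0.111 / 0.139, gives 0.66 / 0.76 / 0.85 SD.

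**The case against.** The strongest reply is that the stated figures do follow from the stated inputs. Months are the only unit the paragraph names. With months and the residual at its maximum share of 1, the results are 83.38 x (0.20 + 1/637.3) = 16.8, giving 17, and 3.35, giving 4 homes. A reader might infer from Step 1 that the residual term was left out. The document does not show that: the match is equally consistent with a month-scale calculation that includes it. This part of the objection stands.

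A reader might also infer that neither trial has 80% power. That too goes further than the document allows, because it depends on one reading of d and on an assumed residual share. No trial enrols 17 per arm. At about 33 per arm, Trial 2 exceeds 80% on the per-year and per-visit scales over the assumed range of r (84 to 98%), and 4 x 10 holds per visit with normal quantiles.

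The definition of d may also be given in the two sources that the paragraph cites, and calling 0.20 conservative is right in direction, since a larger slope variance lowers power.

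What the objection does not rescue is the word medium. The scales on which the sizes survive are those on which d = 0.50 accumulates to 1.25, 2.5 or 15 SD by month 30. Nor is this detail that an article may leave out: the paragraph asserts a definite sample size for a named effect.

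**Conclusion.** The concern holds in this form: the stated sizes equal the slope-variance-only result, and the article does not give the two quantities, time unit and residual share, that decide whether they are adequate. For 17 per condition, either residual variance is negligible (at most about 0.3% if d is the month-30 difference) or d is per month and far from medium. On neither route is 80% power for a medium effect supported.

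The size of the shortfall is conditional. If d = 0.50 SD is the month-30 difference, the 0.20 ratio is on the 0-to-30-month scale and the residual share is 0.3 to 0.7, then 52 to 100 per arm are needed, against about 33 planned in Trial 2, and power is 30 to 57% there and 31 to 53% in Trial 1. On other scales Trial 2 is well powered, but for much larger total differences. Trial 1 has no margin, since its planned 120 is exactly 3 x 4 x 10, and its four homes per arm fall short with a t reference even without residual variance.

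This should be fixed. It concerns what the trials can claim, not whether they can proceed.

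**What to change.** Revise the sample-size paragraph of the Statistical analysis section to:

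1. state the time scale on which d and the variance ratios are defined, for example as the difference at a named visit;
2. state the assumed residual share and include the residual term in the slope variance;
3. use a cluster-level t reference for Trial 1;
4. withdraw 17 per condition and 4 homes as sufficient for a medium effect;
5. give the power, or the difference detectable with 80% power, at the planned sizes (about 33 per arm in Trial 2; 4 x 10 per arm in Trial 1).

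Optionally, drop the description of the 0.20 ratio as conservative, and add a separate figure for cortisol. Cortisol is a primary outcome, but its samples, taken "for two consecutive days, will be obtained at T1-T4 only", cover four visits rather than six.

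The cost is rewording and a short recalculation, with a less favourable power statement as the likely result. Enrolment, design and analysis model stay as they are.
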